### The Eban II intervention

This eight-week, standardized, manualized intervention is facilitated by a male–female team. The intervention (see Table 2) involves: strategies that address the broad array of factors influencing risk behavior among HIV-affected couples; dyadic and group processes that take advantage of relationship and group dynamics; and educational and culturally appropriate sessions [45].

**Table 2 T2:** Core elements of the Eban II intervention

**Sessions**	**Core elements**
**Sessions**	**Principles**
1. ‘Preparing for the Journey’ (Group Session)	Gender, Ethnic, and Cultural Pride
2. ‘Enhancing Couple Communication’ (Couple session)	The Talk and Listen Technique
	Triggers to Risky Behavior
	Learn to Problem Solve with ‘FENCE’
	Identifying Sexual Abuse
3. ‘Tools for the Journey’ (Couple session)	Condom Use
4. ‘Sharing the Load’ (Couple session)	Gender, Ethnic, and Cultural Pride as Couples
5. ‘It Takes a Village’ (Group session)	Reframing Difficult Situations
6. ‘Strengthening the Village’ (Group session)	Self Talk and Relapse Prevention
7. ‘Expanding the Village’ (Group session)	Networking with others and sexual communication with partners
8. ‘Celebrating our Relationship’ (Couple session)	A review of Nguzo Saba principles of unity and rededication to protecting each other

Unlike a traditional RCT, individuals in this study will not be incentivized for attending sessions. However, our experience indicates that incentives enhance attendance and active participation; community agencies frequently provide such incentives to enhance participation in routine programs. Therefore, we will provide minimal participation incentives similar to those often provided routinely by the agencies, such as bus tokens and gift cards at pre-, post-, and three-month follow-up. In addition, usual care, services, and referrals will be available to the WL couples while they wait to enter the risk reduction program. We will learn more about the impact of incentives during sustainability, when these incentives are no longer provided.

### Couples-level data collection procedures

The self-report assessment developed for Eban and pre-programmed into Audio Computer-Assisted Self-Interview (ACASI) [46] takes about 90 minutes to complete. ACASI provides both audio and video presentation of the questions and response options on a laptop computer. ACASI has been shown to significantly decrease social desirability bias [21].

### Implementation-focused evaluation

Several types of assessments will be used to track implementation processes, specifically with regard to fidelity, dose, and intensity of intervention. Throughout the intervention, we will monitor: session attendance, session completion, and participant satisfaction with sessions. Facilitators will also complete short surveys noting adherence to the curriculum, level of participation, specific obstacles that may have arisen, and what components appeared to be most/least appropriate for the session’s participants. Facilitators will also complete overall ratings of each couple’s engagement, competency, and knowledge. To assess fidelity, sessions will be digitally recorded. For the first intervention cohort at each site, all recordings will be reviewed and feedback will be provided to facilitators. Subsequently, a random 15% sample of all session recordings will be reviewed and scored for fidelity to core elements, with a criterion of 80% or more of the total elements considered acceptable [47].

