We operationalize ‘successful implementation’ [36] as a combination of number of couples served (minimum of 18 couples per agency), three completed cycles of the intervention, delivery of the intervention with high fidelity, and high level of satisfaction with the intervention. As noted above, we will also be studying sustainability and cost effectiveness of the intervention for couples. Staff and organizational characteristics will be assessed at all participating CBOs in the first year, and engagement and training will be priorities. Following successful training, implementation of Eban II will commence in two randomly selected CBOs in the first year. The remaining eight CBOs will be phased in randomly with refresher trainings in years two through five. At first glance, it might seem optimal to start all participating agencies at the same ‘baseline,’ but the structure of the funding mechanism makes such a design prohibitive due to the costs associated with implementation in each agency. By limiting training to two to three CBOs per year, we will be able to devote sufficient effort to test whether our implementation approach does in fact contribute to high fidelity implementation. Also, this randomized ‘roll-out’ implementation, or dynamic wait-listed design, has very good statistical properties, including higher power than traditional wait-listed designs [37] and less vulnerability to external, uncontrolled factors [38]. After each of the collaborating agencies completes three eight-week intervention cycles, sustainability will be studied for nine months, during which time only technical assistance will be provided, as discussed further below.

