### Delivery of the Eban II intervention

Agencies will be activated sequentially as cohorts are completed. The flow of agency participation will be as follows: year one, two agencies; year two, two agencies; year three, three agencies; year four, three agencies. All agencies will be required to complete three Eban cycles (eight weeks/cycle). In year five, three-month follow-up evaluation data collection will continue and sustainability will be studied at the agencies that complete the active phase in year four.

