Data regarding acceptability, barriers, and facilitators will be derived from interviews and implementation-focused evaluation measures. As we are examining implementation in 10 large, diverse CBOs, barriers and facilitators will likely vary by agency. The qualitative data will provide the research team with extensive information about acceptability, barriers, and facilitators. In addition, we will examine the facilitator and couples’ satisfaction ratings to characterize acceptability of the intervention. These ratings will be compared both within and across agencies. Potential determinants of adoption and fidelity include but are not limited to training factors, competency at delivering the intervention, types of facilitators (*e.g.*, whether agencies used their own staff as facilitators or used the floating facilitator team), couple ‘mix’ in a given cohort, retention, and satisfaction. All of these factors will be examined when characterizing fidelity across agencies. In addition, based on interviews with facilitators and clients, we will remain open to other determinants that may emerge during implementation. There are several possible determinants of sustainability. We hypothesize that sustainability will be achieved in agencies that have their own trained staff facilitators who deliver the intervention with fidelity and who had positive experiences with the intervention during the implementation phase. To test this hypothesis, we will perform analyses in two levels: (1) Bivariate analyses between sustainability and characteristics of the CBOs and staff. The Pearson Chi-square will be used to test association. ANOVA will be used to test the means of the continuous measures (*e.g.*, ‘the number of agencies that continue to implement Eban II with fidelity’) across the different levels of a categorical measure (‘Does your agency have specific services for high-risk or HIV-positive couples? Yes/no’) at each time point of data collection; (2) Longitudinal analyses for long-term effects. Generalized linear mixed models (GLMM) [67,68] will be used to evaluate the relationship between sustainability and characteristics of the CBOs. GLMM cannot only model global fixed effects (*e.g.*, the number of full-time staff), but also can model random variation (*e.g.*, change over time of individual agency), which is particularly useful.

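### Fidelity sampling after the first cohort is not stratified by agency or session type, so about a quarter of agencies could have no later group session scored

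*Protocol article*

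**What the plan says.** Under Implementation-focused evaluation, recordings are handled in two stages. First, "For the first intervention cohort at each site, all recordings will be reviewed and feedback will be provided to facilitators". Then "a random 15% sample of all session recordings will be reviewed and scored for fidelity to core elements", and 80% or more of the elements counts as acceptable. The first stage is described as review with feedback; scoring and the 80% criterion are mentioned only for the second.

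Table 2 (The Eban II intervention) lists eight sessions with differing core elements. Four are group sessions (1, 5, 6 and 7) and four are couple sessions (2, 3, 4 and 8). Delivery of the Eban II intervention requires three cycles from each agency.

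Overview of study design makes "delivery of the intervention with high fidelity" one component of successful implementation, beside a "minimum of 18 couples per agency". Specific aim two lists possible determinants of adoption and fidelity and says: "All of these factors will be examined when characterizing fidelity across agencies". Under Sustainability, an agency must maintain fidelity to count as having sustained the program.

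**The concern.** A group session is delivered once to the whole group, whereas a couple session is delivered to each couple. In a draw from all recordings, couple sessions therefore dominate, and the number of group sessions scored at any one agency is left to chance. If the draw is pooled over agencies, so is the total number scored at each.

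This matters because fidelity is compared between agencies and related to other agency features, with only ten agencies. If one agency's score rests on couple sessions alone and another's includes two or three group sessions, a difference between them can reflect which sessions were drawn and not how well the program was delivered. Agencies may also differ in how well they run groups and how well they run couple sessions, and an uneven mix hides this.

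**Working it through.** The article gives no number of recordings and no coverage probability, so there is no stated figure to reproduce.

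**Inputs from the article**
- Sampling fraction after the first cohort: 15% (Implementation-focused evaluation).
- Three cycles per agency, so two later cycles (Delivery of the Eban II intervention).
- Four group and four couple sessions per cycle (Table 2).
- 18 couples per agency as a minimum (Overview of study design); 10 agencies.

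**Assumptions, not stated in the article**
- One group per cycle, so each group session gives one recording per cycle.
- One recording per couple for each couple session.
- Couples split evenly over cycles: 18 / 3 = 6 per cycle.
- The 15% sample covers cycles two and three only.

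**Recordings per agency in cycles two and three**
- Group: 2 × 4 = 8.
- Couple: 2 × 4 × 6 = 48.
- Total 56; 15% of 56 = 8.4. Expected group recordings scored: 0.15 × 8 = 1.2.

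**Chance that an agency has no later group session scored**
- 8 of 56 drawn within each agency: C(48,8) / C(56,8) = 377,348,994 / 1,420,494,075 = 0.266.
- 9 of 56 drawn within each agency: 0.221.
- 84 of 560 drawn study-wide: 0.270.
- Approximation, each recording drawn independently: 0.85^8 = 0.272.

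At 0.266, the expected number of agencies affected is 10 × 0.266 = 2.7. The chance of at least one is 1 − (1 − 0.266)^10 = 0.95.

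**Sensitivity to couples per cycle (draw rounded to the nearest whole recording)**

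| Couples per cycle | Recordings per agency | Drawn within agency | P(none), within agency | P(none), study-wide |
|---|---|---|---|---|
| 3 | 32 | 5 | 0.211 | 0.268 |
| 4 | 40 | 6 | 0.236 | 0.269 |
| 5 | 48 | 7 | 0.253 | 0.270 |
| 6 | 56 | 8 | 0.266 | 0.270 |

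**Sensitivity to the other assumptions**
- Two sustainability cycles also in the frame (16 group recordings): 0.85^16 = 0.074.
- Each couple session recorded only once per cycle (16 recordings per agency): 0.264 study-wide; 0.233 or 0.100 within agency with 2 or 3 drawn.

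**Number scored per agency if the draw is pooled**
The count at one agency is hypergeometric (560 recordings, 56 at the agency, 84 drawn). Its mean is 8.4, and its 5th and 95th percentiles are 4 and 13. This spread belongs to a pooled draw only; a draw within each agency fixes the number.

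**After stratification**
With one group session per later cycle taken by design, 2 of 8 group recordings and about 6 of 48 couple recordings are scored per agency. The total stays at about 8, and the chance of no later group session scored falls to 0.

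**The case against.** The strongest case against has four parts.

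1. The article says random, not simple random. A condensed article may leave strata to the full protocol or a fidelity manual. This stands as a caution. But the frame given is all session recordings, and under Progress-focused evaluation the article does name the unit for another check (5% of interviews for each site coordinator and data collector). The ordinary reading is a draw without strata, and nothing else in the text secures coverage.

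2. All first-cohort recordings at each site are reviewed, including all four group sessions. This stands and limits the point. A reader might infer that some agencies have no group session examined at all, or that some core elements are never scored. The article does not support either: every agency has a fully reviewed first cohort, and whether that review produces scores is left open. The gap concerns later cycles. First-cohort scores, if they exist, also come from a period of full review and feedback and cannot show later drift.

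3. There are other fidelity sources: facilitator surveys on adherence, process notes, and tape review during sustainability. This is true, but the surveys and notes are the facilitators' own reports, and the sustainability review is described as technical assistance. The 80% criterion is attached to the 15% sample.

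4. The 27% depends on assumptions about groups per cycle, recordings per couple and which cycles are in the frame. This stands; the figure is a scenario and is reported with its range.

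**Conclusion.** The point holds as a weakness in how the sample is drawn. As written, the 15% rule does not ensure that each agency has a group session scored after its first cohort, or that agencies are scored on a comparable mix. Under the stated assumptions about 27% of agencies, or 2 to 3 of 10, would have no later group session scored. The range is 21–27% for 3 to 6 couples per cycle, and about 7% if the sample also covers two sustainability cycles. A pooled draw would add a spread of roughly 4 to 13 scored recordings per agency.

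The consequence is limited to fidelity comparisons between agencies. The couples' effectiveness outcomes are not touched. It is a modest improvement to make, not a flaw that threatens the trial.

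**What to change.** - Draw the same 15% stratified by agency and session type, with at least one group and one couple session per later cycle at each agency.
- Rotate which of the four group sessions is drawn, so that different ones are covered over cycles and agencies.
- When reporting agency fidelity, weight back to the session mix. With 2 of 8 group and 6 of 48 couple recordings scored, each group recording stands for 8 / 2 = 4 recordings and each couple recording for 48 / 6 = 8.
- Score the first-cohort recordings, which are reviewed anyway, on the same checklist, or state that they are scored. Report them apart from later cycles.
- State whether the sample extends to the sustainability cycles.

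The cost is a sampling list, simple weights and a little extra scoring of recordings already reviewed; the number reviewed stays about the same. One limit remains: one group session per later cycle covers at most two of the four group sessions at an agency. The change secures a comparable session mix but does not guarantee that every group session's core elements are scored in cycles two and three.

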### Progress-focused evaluation

At the organizational level, this component will involve assessing the monthly SCIN conference calls. Minutes of all calls will be maintained (including attendance rosters), as will minutes from all project-related meetings. Regarding progress at the couples-level, this component will involve weekly calls between the regional project managers and the site coordinators. A periodic onsite review of procedures at each site will be conducted, and a random selection of 5% of pre- and post-test and follow-up interviews for each site coordinator and data collector will be reviewed to ensure that the protocol is administered in a standardized fashion.

### Cost assessment

The cost of the delivered services will be calculated using a customized cost-analysis spreadsheet which uses state of the art recommendations for cost analysis as articulated by the US Panel on Cost-Effectiveness in Health and Medicine [48]. The cost analysis data will be collected by the data collectors and sent on a quarterly basis to the management team, and reviewed with the cost consultant in quarterly conference calls to analyze the cost information, identify trends, and solve any problems with data collection.

### Phase four: practice improvement

Phase four involves interpretive evaluation, assessment of sustainability, and a project retreat. Because this project will occur in waves, practice improvement will be examined after each agency completes the active intervention phase (delivery of the groups and completion of three-month follow-up). Sustainability will be examined for nine months following the completion of the required three groups and follow-ups.

### Interpretive evaluation

Key stakeholders will have completed interviews regarding their satisfaction with Eban II during active implementation, and their expectations regarding sustainability and cost effectiveness. Following sustainability, these stakeholders will be re-interviewed.

### Sustainability

We define the sustainability phase as beginning after the active implementation phase is completed at each site (*i.e.*, baseline through the 3-month follow-up). At this point, the reliance on grant funds ends and sites will be encouraged to integrate Eban II into their usual services. At each site, the nine-month sustainability period will be preceded by a pre-sustainability workshop to identify and address any issues that the agencies perceive to be barriers [49]. During sustainability, Eban II will be delivered in the CBOs with trained staff serving as co-facilitators, supported by technical assistance (including quality assurance) from the management team. Technical assistance will include retraining in the intervention, sharing resources, offering suggestions on lessons learned, and review of session tapes to assess fidelity. Agencies that discontinue participation during this phase will be contacted to encourage participation and/or to identify the reasons for discontinuation. Agencies that independently deliver two eight-week cycles of the intervention with two to three couples in each cycle and maintain fidelity to the intervention core elements will be considered to have achieved sustainability. Pre-post couples-level measures will also be collected in order to examine outcomes. Sustainability will be assessed by documenting the number of couples that each agency recruited and enrolled in Eban II; the number of couples who completed the intervention; and how much technical assistance they needed and received.

### Project retreat

Additional funds will be sought to support a project retreat for the management and implementation teams to come together with additional representatives from the SCIN to discuss preliminary findings and the future of the intervention. Individuals from interested agencies that were not part of the original 10 CBOs will be invited to attend a designated portion of this retreat, and a structured discussion guide will be used to explore likelihood of adoption, perceived need for the intervention, preliminary perceptions of the program, and its trialability.

### Measures to be completed by staff

An electronic Staff Survey will capture basic demographics of staff (~20 per agency) including education level and professional experience. The 50-item Evidence-Based Practices Attitudes Scale (EBPAS) [50] will be used to assess staff attitudes toward evidence-based practices. The widely used Maslach Burnout Inventory (MBI; Maslach) [51] will be used to assess staff experience of workload. Subscales from the TCU Survey of Organizational Functioning (TCU SOF) [52] will be used to assess motivational factors, program resources, staff attributes, and organizational readiness. All subscales of the SOF have demonstrated good internal consistency and validity [53].

In addition to these structured measures, semi-structured interviews will be conducted with a subset of key stakeholders (approximate n = 50; five per agency). Process-focused interviews will include questions about feasibility, satisfaction, perceived fidelity, barriers, desired revisions, perceived cost-effectiveness, and expectations for sustainability. Sustainability-focused interviews will include similar questions, but will refer to the sustainability period and their satisfaction with and future expectations of the utility and cost-effectiveness of Eban II as a long-term option for agencies’ usual menu of services.

### Cost analysis measures

We will use a cost-analysis spreadsheet approach to measure the cost of HIV prevention, case management, and adherence services for CBOs providing front-line services. The spreadsheet incorporates key cost analysis principles, calculates the cost per client of HIV/AIDS services delivered, and also conducts threshold analyses to set performance standards for how many HIV infections would have to be averted for Eban II to be considered cost-saving or cost-effective to society.

### Measures to be completed by clients

Primary behavioral and physiologic outcomes are as follows:

1. Percentage of condom-protected sexual acts in the past 90 days.

2. Number of episodes of unprotected sexual intercourse.

3. Number of sexual partners.

4. Types of partners (primary, casual, new).

5. Frequency of oral, anal, and vaginal sex.

6. Use of alcohol and other drugs prior to sexual intercourse.

7. Partners’ risk status (*e.g.*, sexual partner has other partners).

We will also track concurrency, seroconversion, and incident STIs. In order to control for response bias, several steps will be taken, including: assessing sexual behaviors over a relatively brief period (*i.e.*, past three months at baseline and follow-ups and past seven weeks at post-intervention); providing participants with a calendar for benchmarking salient dates; involving only trained data collectors in the data collection; using the ACASI; and administering a five-item measure of social desirability bias [54].

Potential covariates include demographic characteristics; mental health status as measured by the 45-item Brief Symptom Inventory (BSI); history of sexual abuse as measured by the Wyatt Sex History Questionnaire (WSHQ) [55]; and history of physical abuse as measured by the 19-item Revised Conflict Tactics Scale (CTS) [56], which assesses both history and recent (*i.e.* past 90 days) experiences of abuse. Hypothesized mediators [57] include condom use self-efficacy, which has been linked to effective condom use [58,59], as measured by the Condom Use Self-Efficacy Scale [60]; condom communication self-efficacy as measured by a nine-item scale measuring confidence in negotiating the use of a male condom [60]; and couples’ sexual communication skills as measured by a seven-item scale on the level of reported comfort on safer sex communication items [61]. Moderators include several variables identified in Eban I as likely to moderate intervention effects [57]: the length of the couple’s relationship, because those in longer relationships are less likely to practice safer sex [45]; relationship satisfaction will be assessed with the Dyadic Adjustment Scale [62], which asks how partners relate to each other about family finances, time spent together, relational factors, and intimacy; substance use/abuse (frequency and amount of alcohol use each day in the past three months and age of first use) as measured by the CAGE [63] to assess dependence on alcohol, and section B of the NIDA Risk Behavior Assessment (RBA) [64] to assess the frequency, modality, and level of use of licit and illicit drugs in the past month.

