**Methods/design:**

This hybrid implementation/effectiveness implementation study is guided by organizational change theory as conceptualized in the Texas Christian University Program Change Model (PCM), a model of phased organizational change from exposure to adoption, implementation, and sustainability. The primary implementation aims are to assist 10 community-based organizations (CBOs) to implement and sustain Eban II; specifically, to partner with CBOs to expose providers to the intervention; facilitate its adoption, implementation and sustainment; and to evaluate processes and determinants of implementation, effectiveness, fidelity, and sustainment. The primary effectiveness aim is to evaluate the effect of Eban II on participant (n = 200 couples) outcomes, specifically incidents of protected sex and proportion of condom use. We will also determine the cost-effectiveness of implementation, as measured by implementation costs and potential cost savings. A mixed methods evaluation will examine implementation at the agency level; staff members from the CBOs will complete baseline measures of organizational context and climate, while key stakeholders will be interviewed periodically throughout implementation. Effectiveness of Eban II will be assessed using a randomized delayed enrollment (waitlist) control design to evaluate the impact of treatment on outcomes at posttest and three-month follow-up. Multi-level hierarchical modeling with a multi-level nested structure will be used to evaluate the effects of agency- and couples-level characteristics on couples-level outcomes (*e.g.*, condom use).

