### Primary effectiveness aim

#### Aim three

To evaluate the effect of intervention implementation on participant outcomes, specifically incidents of protected sex and proportion of condom use.

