### Sample size calculation and power analyses

Sample size calculation and power analyses were conducted at both the agency- and couple-levels to ensure that we have sufficient statistical power for all analyses. At the agency level, the power analysis was based on the comparisons of key measures from providers (*e.g.*, provider attitudes toward evidence-based practices). From the 10 selected agencies, we will collect data from 100 non-clerical staff (10 providers per agency) in order to provide sufficient power to examine the within- and between-agency variation. With a type I of 0.05, type II error of 0.2 (or power of 80%), intra-agency correlation at 0.15 level, 100 raters from the 10 agencies will enable us to detect an effect size as small as 0.9 in standard deviation unit for measures from staff [65,66]. Non-parametric and parsimonious models will be used to accommodate the limitation of a relatively small number of agencies.

At the couples level, calculations were carried out based on the comparison of key outcome measures of incidents of unprotected sex and an increase in the proportion of condom use (*i.e.*, the number of times condoms were used during intercourse divided by the number of times sexual intercourse is reported) between intervention and waitlist control. With a repeated measures design, type I error 0.05, type II error 0.20, intra-couple correlation 0.4, the mean number of available repeated measures 2.5 (from baseline, post and three-month measurements), and a 2:1 ratio of intervention and waitlist control, a total of 174 couples would allow us to detect an effect size as small as 0.30 in standard deviation unit for number of unprotected sexual intercourse acts [65,67]. Thus, our planned sample of 180 couples provides sufficient power.

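### The primary effectiveness outcome is stated inconsistently (protected acts, unprotected acts, seven primary items), and the power claim holds only for one outcome at 0.05

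*Protocol article*

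**What the plan says.** Four places in the protocol article bear on which outcome decides effectiveness.

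- **Abstract (Methods/design) and Aim three.** Both name two outcomes: "specifically incidents of protected sex and proportion of condom use".
- **Sample size calculation and power analyses.** The couples-level calculation rests on "key outcome measures of incidents of unprotected sex and an increase in the proportion of condom use", with the proportion defined as "the number of times condoms were used during intercourse divided by the number of times sexual intercourse is reported". The only detectable effect given is 0.30 SD for the number of unprotected acts: 174 couples, type I error 0.05, 80% power, 2:1 allocation. The planned 180 couples are then called sufficient.
- **Measures to be completed by clients.** Seven items follow the words "Primary behavioral and physiologic outcomes are as follows". The first two are "Percentage of condom-protected sexual acts in the past 90 days" and "Number of episodes of unprotected sexual intercourse". The other five are number of partners, types of partners, frequency of three kinds of sex, substance use before sex, and partners' risk status.
- **Data analysis plan, Specific aim three.** Repeated-measures and hierarchical models are planned for behavioral and psychosocial outcomes in general. No single primary outcome is named.

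**The concern.** The article gives three answers to the question of which outcome is primary. The count named in the aim (protected acts) is neither the count that was sized nor an item on the primary list. The aim has two outcomes and the list has seven. The type I error of 0.05 and the 80% power are stated once, with a detectable effect for one outcome.

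Two things are at stake. First, a count of protected acts rises or falls with total sexual activity, so it can move against the benefit the trial seeks. Second, the stated error rate and power are tied to a single test. If two or seven outcomes are all primary, then either the error rate exceeds 0.05 or power falls below the claimed level. The choice matters now because the article says data collection is under way but cleaning and analysis have not begun. The outcome can still be named without any suspicion that results guided the choice.

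**Working it through.** **1. Are the two counts interchangeable?** Unprotected acts = total acts − protected acts, so they are complements only if the total is fixed. Take an illustrative couple:

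| | Total | Protected | Unprotected | Proportion |
|---|---|---|---|---|
| Before | 20 | 10 | 10 | 50% |
| After | 8 | 8 | 0 | 100% |

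The protected count falls from 10 to 8, which is worse on a literal reading of Aim three. The unprotected count and the proportion both show full benefit.

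**2. Reproducing the plan's 174.** Inputs from the sample size section: 0.30 SD, α = 0.05, power 0.80, ratio 2:1, correlation 0.4, mean of 2.5 measures. Sidedness is not stated; two-sided is assumed.

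- Without correlation gains: total N = 3 × (1 + 1/2) × ((1.960 + 0.842)/0.30)² = 392.4.
- Repeated-measures factor: (1 + 1.5 × 0.4)/2.5 = 0.64.
- Two-partner factor: (1 + 0.4)/2 = 0.70.
- 392.4 × 0.64 × 0.70 = 175.8, so 176, close to 174.

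This assumes that the single 0.4 applies both between partners and over time, which the article does not state. Without the partner factor, the result is 252 (two-sided) or 198 (one-sided), and neither matches. One-sided testing with 1:1 allocation also gives 176, but contradicts the stated 2:1. In the matching reading, 174 is the figure for one outcome at an unadjusted 0.05.

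**3. Power if 0.05 is shared.** This step takes the plan's own statement (174 couples, 80% power) as given. It assumes an effect of 0.30 SD on each outcome. For q outcomes under Bonferroni:

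- Power at N = Φ((1.960 + 0.842) × √(N/174) − z), where z is the normal quantile at 1 − 0.05/(2q).
- N for 80% power = 174 × ((z + 0.842)/(1.960 + 0.842))².

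| q | z | N for 80% | Power at 174 | Power at 180 | Detectable effect at 174 |
|---|---|---|---|---|---|
| 1 | 1.960 | 174 | 80% | 81% | 0.30 SD |
| 2 | 2.241 | 211 | 71% | 73% | 0.33 SD |
| 7 | 2.690 | 277 | 54% | 56% | 0.38 SD |

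**4. Error rate if 0.05 is not shared.** With independent tests, the chance of at least one false positive is 1 − 0.95² = 9.75% for two and 1 − 0.95⁷ = 30.2% for seven. For equally correlated normal test statistics (simulation, 400,000 draws):

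| Correlation | Two outcomes | Seven outcomes |
|---|---|---|
| 0.3 | 9.5% | 27% |
| 0.5 | 9.1% | 23% |
| 0.8 | 7.9% | 15% |

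**5. Would a three-month-only primary keep the sample size?** No. Dropping the repeated-measures factor gives 392.4 × 0.70 = 274.7, about 275 couples. Adjusting for baseline at correlation 0.4 gives 274.7 × (1 − 0.4²) = 230.8, about 231. Power at 174 would be about 61% or 68%. This step depends on the reading in step 2.

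**The case against.** The strongest reply is that the intent is plain. The sample size, item 2 of the primary list, the eligibility rule and the earlier efficacy trial's result all concern unprotected sex. The word protected in the abstract and Aim three is then probably a slip. That is likely right, and it limits the point. A reader might infer that the direction of benefit is open throughout, but the sample size section fixes it for the proportion as an increase. What stands is that the slip, if it is one, sits in both the abstract and the primary effectiveness aim, and that seven items still carry the label primary.

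A second reply is that multiplicity rules usually belong in an analysis plan, which is not shown. This also stands: the absence of a rule is not the point. A reader might take 30% as the trial's actual false-positive risk, or reach 51% by counting seven items at two visits (1 − 0.95¹⁴). The article nowhere says each item will be tested separately at 0.05, and it plans models that use the visits jointly. Several items, such as types of partners, have no single summary to test. The percentages show what depends on the unresolved choice; they do not forecast the error rate.

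Third, the proportion is undefined for a couple reporting no intercourse, and a reader might infer that such couples are dropped after randomisation. The article does not say so. Handling of a zero denominator can be settled in an analysis plan, and partners remaining after a break-up are still followed.

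An unseen analysis plan could choose one outcome, but it could not make these sections of the article agree.

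**Conclusion.** The point holds as an inconsistency in the article's own text. The aim's count is not the one that was sized or listed, two outcomes in the aim become seven in the measures section, and no statement says which outcome the 0.05 covers.

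The claim of sufficient power at 180 couples is sound for one outcome at 0.05 (about 81% on the plan's own basis). It falls to about 73% if two outcomes share the error rate by Bonferroni and about 56% if seven do. Without adjustment, family-wise error would be about 8–10% for two outcomes or 15–30% for seven, over correlations from 0.8 down to 0.

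These figures assume two-sided testing and equal standardised effects. The power figures are anchored to the article's 174 couples and do not depend on how that number was derived. The documents do not support a stronger conclusion, whether that the direction of benefit is undefined in general, that a 30% or 51% error rate is planned, or that couples are excluded from the proportion.

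**What to change.** - In the abstract and Aim three, replace incidents of protected sex with number of unprotected sexual acts.
- Name that count as the single primary effectiveness outcome at 0.05. Analyse it with the planned repeated-measures model using baseline, posttest and three-month data, so that the basis of the 174 couples is kept. The client measures section gives recall of seven weeks at posttest and three months otherwise, so state how the count is put on a common time scale.
- Make the condom proportion the key secondary outcome, tested only if the primary succeeds.
- Relabel the other five items in the client measures section as secondary.

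The three-month count alone should not be made primary without resizing the trial, for the reason in step 5 of the working.

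The cost is wording in the protocol and analysis plan. The sample size and data collection are unchanged. Six outcomes, including the condom proportion, lose the label primary, and the proportion can be claimed only after success on the count.
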